## Abstract

**Introduction::**

Atrial fibrillation (AF) is the most common cardiac arrhythmia and increases the risk of ischemic stroke 4 to 5-fold. The first choice of anticoagulant therapy (AT) is the vitamin K antagonist (VKA). Contraindication to VKA or poor control of the International Normalized Ratio leads to the administration of direct-acting oral anticoagulants. There is a trend toward inadequate AT in nonvalvular AF (NVAF) patients. Aim: To evaluate the impact of the implementation of a decision support tool linked to the digital clinical history on the adequacy of AT, the incidence of complications, and the mortality in patients with NVAF in primary care centers (PCCs) of the Catalan Institute of Health (ICS).

**Methods and analysis::**

Randomized clinical trial in 287 PCCs, formed by 2 groups (intervention and control). Population: patients controlled in PCCs, diagnosed with NVAF 1 year before the implementation of the decision support tool and with VKA treatment over a minimum of 1 year. A simple randomization method will be performed at a sector level. The decision support tool will be available for 1 year. The time in therapeutic range (TTR) will be available in the digital clinical history only to professionals of the intervention group. The information system for primary care research development database will be used for the data extraction. Statistical analysis will be done at 3 time points: before the implementation of the tool, at 1 year, and at 2 years after the beginning of the intervention. Multilevel (patient and professional levels) logistic regression models will be used to estimate the effect of the intervention.

**Ethics and dissemination::**

This study protocol was approved by the Ethical Committee of Clinical Investigation of the *Institut Universitari d’Investigació en Atenció Primària Jordi Gol* (code P17/091). Articles will be published in scientific journals.

**Trial registration::**

Clinical-Trials.gov: NCT03367325.

## Introduction

1

Atrial fibrillation (AF) is the most frequent type of cardiac arrhythmia, and patients with AF have a 4 to 5-fold greater risk of ischemic stroke than the general population.^[1,2]^ This arrhythmia affects more than 6 million people in the European Union, with an estimated prevalence of 1.5% to 2% in the general population, increasing to up to 24.4% in individuals of more than 85 years of age.^[1,3–5]^

According to the European Heart Rhythm Association, nonvalvular AF (NVAF) is produced in the absence of mechanical prosthetic heart valves and the absence of moderate to severe mitral stenosis.^[6]^ NVAF carries an increased risk of death, morbidity, and hospitalization with the subsequent increase in healthcare costs.^[1,7–9]^ Although the physiopathology of NVAF is well-known, the diagnosis and management of these patients needs to be improved.^[10]^ The main objective of the management of these patients is to reduce the symptoms and prevent the severe complications associated with this arrhthymia. The prevention of thromboembolic complications is based on antithrombotic treatment with either oral anticoagulants or antiplatelet drugs.^[1,8]^

Vitamin K antagonists (VKAs) were the only oral anticoagulants available for many years. However, the characteristics of VKAs may make their use in patients with NVAF challenging in clinical practice, leading to difficulties in the management of these patients and the need to adapt the therapy.^[11]^ Recently, direct-acting oral anticoagulants (DOACs) were developed and have shown to be safe and effective in the prevention of stroke and systemic embolism in patients with NVAF, although some limitations have also been reported.^[12]^

Since the introduction of DOACs in Spain their use has been on the rise. Nevertheless, data from the Catalan Health Service on the adequacy of DOAC prescriptions indicate that according to the recommendations of the pharmacotherapy commission more than 25% of the patients are not candidates for dabigatran treatment and are receiving it, whereas patients who are candidates to this treatment are not receiving the drug.^[13]^ These results indicate a clear problem of adequacy to the anticoagulant treatment. We believe that this problem is probably because of the absence of any single variable in the electronic clinical history of the Catalan Institute of Health (ICS) that provides direct knowledge regarding control of the international normalized ratio (INR), thereby making it difficult to know the real level of control in the previous 6 months, and consequently, the adequacy of treatment and the possible changes needed.

The present project has been designed taking into account the above situation. The aim of the project is to improve the information available in the electronic clinical history by direct calculation of the time in the therapeutic range (TTR) once the value of the last INR of NVAF patients receiving VKA has been entered. When the TRT is < 65% at 6 months, an alert will be activated and will inform the professional of the need to evaluate a change in the treatment. The TTR (calculated using the Rosendaal method^[14]^) is a widely applied measure for the evaluation of the adequacy of anticoagulant therapy (AT) with VKAs. In several guidelines on the management of AF the TTR is used as a treatment control criterion, although the use of these guidelines are not generalized throughout the world.^[15]^ According to the recommendations of the ministry of health, social services and equality of Spain (based on the National Institute for Health and Care Excellence guideline^[16]^) for the use of DOAC in NVAF patients, a TTR <65% is a criterion of poor VKA control.^[11]^

Despite the increasingly more frequent use of computerized medical reminders, few studies have assessed their impact on health outcomes.^[17–21]^ A systematic review showed that notifications influence specific aspects of the prescription process and may be an effective method to reduce the prescription of contraindicated medications, although their impact on health outcomes was not demonstrated.^[22]^ Within the primary care setting it was found that computerized clinical notifications significantly improved the adequacy of treatment in patients with poorly controlled asthma and consequently reduced the rate of reexacerbations during follow-up. Moreover, medical professionals considered these reminders to be particularly useful for the identification of patients with bad control.^[23]^

The present project aims to evaluate the impact of the implementation of a clinical decision support tool associated with the electronic clinical history which informs healthcare professionals of the TTR in patients with NVAF attended in primary care centers (PCCs) of the ICS. This project will evaluate the impact of this tool on the adequacy of anticoagulant treatment, the incidence of thromboembolic and hemorrhagic complications, and mortality at 2 years after the beginning of the intervention. The evaluation of the impact of the intervention will be performed based on the characteristics of the patients and the healthcare professionals.

## Methods and design

2

### Study design and setting

2.1

A cluster, randomized, clinical trial (type: parallel group) will be performed with patients attended in the ICS primary care setting. It is estimated that 5.8 million people are attended in ICS which comprises 287 PCCs around Catalunya (source: Sistemes d’Informació dels Serveis d’Atenció Primària (SISAP) of the ICS, unpublished data).

### Participants

2.2

The study will be carried out in patients diagnosed with NVAF receiving anticoagulant treatment.

#### Inclusion criteria (all criteria must be met)

2.2.1

Patients diagnosed with NVAF 1 year prior to the implementation of the computerized tool;Patients receiving anticoagulant treatment with DOACs or VKAs;Patients followed in primary care (with at least 6 INR controls during the year prior to the intervention). The restriction related to the INR controls is to minimize the variability in INR at the initiation of treatment and avoid the effect that temporary withdrawal of VKA anticoagulants might have on the percentage of good INR control.

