### Intervention

2.3

The clinical decision support tool for improving the adequacy of AT in NVAF (CDS-NVAF) was developed by the ICS in collaboration with primary care physicians in 2017. CDS-NVAF is intended for patients diagnosed with NVAF and treated with VKA. This tool calculates the TTR using the Rosendaal method considering the last INR data. The INR data are found in the clinical history of NVAF patients and are located on the screen of the follow-up of oral anticoagulant use.

The CDS-NVAF will be activated when the physician introduces the last INR value. At this time the TTR will be calculated automatically. If the TTR value is <65%, a pop up screen with an advisory text will open suggesting a change to DOAC therapy. The physician can decide whether to change or not the previous prescription. If the TTR value in >65% the pop up screen will not appear. The TTR value will remain registered on the screen of the follow-up of oral anticoagulant use and can be consulted in future queries.

The diffusion of the CDS-NVAF will be made by an announcement on the first day of the intervention when the healthcare professional opens the electronic clinical history. The professionals of the intervention group will receive the announcement and will be provided with the CDS-NVAF. The professionals who are part of the control group will not receive any of the above described information.

The implementation of the CDS-NVAF, and thus, the beginning of the study is expected to December 15, 2017.

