### Sample size

2.4

In a first approach the information system for primary care research development (SIDIAP) established that during 2015 PCCs of the ICS had registered 171,472 cases of NVAF, 73,632 of whom were receiving anticoagulant treatment (63,001 VKAs and 10,631 DOACs). Assuming a weight of 90%, an alpha error of 5%, a control versus intervention ratio of 1, corrected for the design by clusters and assuming a loss of 10%, our study will be able to detect a difference of 1% for a rate of thromboembolic events of 0.66%. Despite this power, a clinically relevant relative reduction of 10% will be established.

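### The eligible population is defined in conflicting ways: VKA for at least 1 year in the abstract, DOAC or VKA in section 2.2.1, for a tool that acts only on VKA patients

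*Protocol article*

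**What the plan says.** Five places in the protocol article bear on who is in the trial.

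- **Abstract, Methods and analysis:** patients with NVAF diagnosed a year before launch and "with VKA treatment over a minimum of 1 year".
- **Section 2.2, Participants:** "patients diagnosed with NVAF receiving anticoagulant treatment", with no restriction on the drug.
- **Section 2.2.1, Inclusion criteria,** under the rule that "all criteria must be met": the second criterion is "Patients receiving anticoagulant treatment with DOACs or VKAs", with no minimum duration. The third requires follow-up in primary care "with at least 6 INR controls during the year prior to the intervention". Its stated reasons concern unstable INR at the start of treatment and temporary interruption of VKA.
- **Section 2.3, Intervention:** "CDS-NVAF is intended for patients diagnosed with NVAF and treated with VKA". The trigger is also fixed: "The CDS-NVAF will be activated when the physician introduces the last INR value". A pop-up follows if the calculated TTR is below 65%.
- **Section 2.4, Sample size:** of the NVAF cases registered in 2015, "73,632 of whom were receiving anticoagulant treatment (63,001 VKAs and 10,631 DOACs". The section does not say which of these counts entered the calculation.

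The last paragraph of the Discussion concedes that the tool does not inform on the adequacy of DOAC treatment and asks that this be kept in mind when results are read.

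**The concern.** Eligibility decides the denominator of every primary outcome. Here two readers could extract two different cohorts from the database and each could cite the protocol. Section 2.2.1 also pulls against itself: one criterion names DOACs, and the next requires a level of INR monitoring that is explained only in terms of VKA.

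Who is included matters because the intervention works through the INR screen. A patient on a DOAC at launch, for as long as that continues, has no route to the alert in either arm. Such patients would pull the contrast in thromboembolic events, haemorrhage and death towards zero.

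They would also affect the adequacy outcome. Section 2.8.1 and Table 2 score maintained treatment as adequate or inadequate, so baseline DOAC users would contribute zeros and ones on prescribing that the tool does not address. The Introduction reports that more than 25% of patients are not candidates for dabigatran yet receive it, so these scores need not be uniform.

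**Working it through.** **1. The definitions side by side.** The abstract's VKA requirement is read as current treatment at launch.

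| Patient at launch | Abstract | Section 2.2.1 | Can trigger the tool |
|---|---|---|---|
| VKA for 1 year or more, six or more INRs | in | in | yes |
| VKA for under 1 year, six or more INRs | out | in | yes |
| DOAC after a recent switch from VKA, six or more INRs | out | in | no |
| Established DOAC user, fewer than six INRs | out | out | no |

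The definitions disagree on rows 2 and 3. Row 3 is where unexposable patients enter.

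**2. The plan's own figures.** The split in section 2.4 adds up: 63,001 + 10,631 = 73,632. The stated detectable difference of 1% cannot be reproduced, because neither the N nor the cluster correction is given, nor whether the 1% is absolute or relative.

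**3. Dilution.** Let *s* be the share of analysed patients on a DOAC at baseline. Assume no effect in them and the same event rate as in VKA users. The overall relative effect is then (1 − *s*) times the effect in VKA users, and the required sample grows by about 1/(1 − *s*)².

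- Largest *s* on the 2015 counts: 10,631/73,632 = 0.144.
- Effect factor: 1 − 0.1444 = 0.856.
- Sample factor: 1/0.8556² = 1.37.
- If no DOAC user passes the six-INR rule: *s* = 0, and both factors are 1.

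The documents do not give the number of recent switchers, so the true value lies between these ends and cannot be located.

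**4. Consequence for section 2.4.** Inputs from section 2.4: 10% loss, 1:1 allocation, event rate 0.66%, alpha 5% (taken as two-sided), and 90%, which the article calls a weight and is read here as power. The design effect is set to 1 because none is given. The sample size per arm is

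n = [1.96·√(2p̄(1−p̄)) + 1.2816·√(p₁(1−p₁)+p₂(1−p₂))]² / (p₁−p₂)²

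| | All anticoagulated | VKA only |
|---|---|---|
| Base | 73,632 | 63,001 |
| Per arm after loss (base × 0.9/2) | 33,134 | 28,350 |
| Detectable relative reduction at 90% power | 28.6% | 30.7% |
| Power for a 10% reduction in VKA users, none in DOAC users | 14.9% | 16.7% |

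In the left column of the last row the overall effect is 10% × 0.856 = 8.6%. Had DOAC users benefited equally, power there would be 18.8%.

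The 10% relative reduction that section 2.4 calls clinically relevant (0.66% to 0.594%) needs about 300,600 per arm before any cluster correction. Neither population comes near it. If the 1% is read as an absolute difference (0.66% against 1.66%), 2,408 per arm suffice before clustering, and both populations allow a large design effect: 33,134/2,408 = 13.8 and 28,350/2,408 = 11.8. Which population is used does not alter the conclusion under either reading.

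**The case against.** The strongest reply is that the six-INR criterion already does the work. All inclusion criteria must hold together, so most established DOAC users fail and few unexposable patients remain. This stands as far as size goes. A reader might infer that 14.4% of the analysed patients cannot be exposed; the documents do not support that, because section 2.2.1 largely prevents it. It does not remove the contradiction, since recent switchers and short-term VKA users are still classified differently by the abstract and section 2.2.1.

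A second reply is that section 2.4 only describes the registered population. That also stands. A reader might infer that DOAC users were counted in the sample size, but the section gives a total and a split and never names the N used. The 33,134 per arm above is a construction for comparison, not a protocol figure.

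Third, the limitation is disclosed, and inappropriate DOAC prescribing is part of the problem the trial describes. A wider anticoagulated population could therefore be a deliberate, diluted real-practice target. That is a defensible choice if it is made. The Discussion's caveat does not make it: it neither reconciles the definitions nor says whether baseline DOAC users are analysed.

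Finally, a reader might go further and calculate how large the effect must be among patients with TTR below 65%. The documents give no share of VKA patients below that threshold. Such a figure would also assume equal event rates above and below it, and would ignore that professionals in the intervention group see the TTR whatever its value. It is not part of this point.

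**Conclusion.** The contradiction is real and stands in the current text. The abstract and sections 2.2 and 2.2.1 define different cohorts, and section 2.2.1 names a drug class that its own INR criterion mostly excludes and that the tool does not act on. Every primary estimate depends on which definition the extraction applies.

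The size of any dilution is unknown. The upper bound is a factor of 0.856 on the effect and about 1.37 on the sample. It assumes no effect and equal event rates in DOAC users, all of them analysed, and the 2015 drug split. The Introduction says DOAC use is rising, so the split at launch may differ.

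This point does not show that the sample-size conclusion is wrong because of DOAC users. Moving from 28.6% to 30.7% in the unclustered detectable reduction is small, and the 10% target is out of reach with either population. Nor is the lack of an analysis restricted to baseline TTR below 65% an error; it would be an optional addition.

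**What to change.** Before data extraction, use one definition in the abstract and in sections 2.2, 2.2.1 and 2.4:

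- Restrict the primary analysis set to patients on a VKA at the start date who meet both the 1-year and the six-INR criteria.
- Apply the drug criterion at baseline only. Patients switched to a DOAC after the start stay in, since switching is how the intervention is expected to act.
- Describe any baseline DOAC users separately, outside the primary estimate.
- State in section 2.4 the N used, which on the 2015 counts is at most 63,001 (28,350 per arm after 10% loss). The 1-year and six-INR criteria will lower it further.

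If the sponsor prefers the wider population, the text should say so in all of these places and reconcile the six-INR criterion with it.

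The cost is some rewording and one filter in the extraction. The downside is a smaller stated sample and results that apply to a narrower population.

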#### Exclusion criteria

2.2.2

Patients with INR control in the reference hospital;Patients with valvular AF (mitral stenosis);Patients with a prosthetic heart valve;Change to another PCC.

### Intervention

2.3

The clinical decision support tool for improving the adequacy of AT in NVAF (CDS-NVAF) was developed by the ICS in collaboration with primary care physicians in 2017. CDS-NVAF is intended for patients diagnosed with NVAF and treated with VKA. This tool calculates the TTR using the Rosendaal method considering the last INR data. The INR data are found in the clinical history of NVAF patients and are located on the screen of the follow-up of oral anticoagulant use.

The CDS-NVAF will be activated when the physician introduces the last INR value. At this time the TTR will be calculated automatically. If the TTR value is <65%, a pop up screen with an advisory text will open suggesting a change to DOAC therapy. The physician can decide whether to change or not the previous prescription. If the TTR value in >65% the pop up screen will not appear. The TTR value will remain registered on the screen of the follow-up of oral anticoagulant use and can be consulted in future queries.

The diffusion of the CDS-NVAF will be made by an announcement on the first day of the intervention when the healthcare professional opens the electronic clinical history. The professionals of the intervention group will receive the announcement and will be provided with the CDS-NVAF. The professionals who are part of the control group will not receive any of the above described information.

The implementation of the CDS-NVAF, and thus, the beginning of the study is expected to December 15, 2017.

### Sample size

2.4

In a first approach the information system for primary care research development (SIDIAP) established that during 2015 PCCs of the ICS had registered 171,472 cases of NVAF, 73,632 of whom were receiving anticoagulant treatment (63,001 VKAs and 10,631 DOACs). Assuming a weight of 90%, an alpha error of 5%, a control versus intervention ratio of 1, corrected for the design by clusters and assuming a loss of 10%, our study will be able to detect a difference of 1% for a rate of thromboembolic events of 0.66%. Despite this power, a clinically relevant relative reduction of 10% will be established.

### Randomization

2.5

The randomization will be made by sectors of the ICS. A sector is a group of PCCs that share 1 computer server. The ICS has 15 sectors. The sectors will be randomized using a simple randomization method. From the generation of random numbers (between 0 and 1) 2 groups will be created so that the numbers with which the first decimal is <5 will be rounded down to 0 and the remaining will be rounded up to 1. The sectors associated with 0 will constitute the control group and those associated with 1 will make up the intervention group. The study flowchart is presented in Figure 1.

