### Statistical analysis

2.10

The statistical analysis will be performed at 3 time points: before the implementation of the CDS-NVAF (baseline), at 1 year after the beginning of the intervention (1-year follow-up), and at 2 years after the beginning of the intervention (2-year follow-up).

A descriptive analysis of all the variables studied will be carried out using frequency and percentage for categorical variables and mean, standard deviation, minimum, median, and maximum for continuous variables. The Students’ *t* test (or the Mann–Whitney U test in cases not fulfilling the criteria of normality) will be used to determine possible differences in the means of the quantitative variables between the 2 study groups. The Chi-square test (or Fisher exact test) will be used for the qualitative variables. The rates of incidence for each variable will be expressed as patient/years with the corresponding confidence intervals of 95%.

Analysis at a professional level: a logistic regression model will be used to search for possible associations among the primary outcome variables and the secondary variables. First, each variable will be evaluated separately by univariate models and all the variables that are statistically significant or have a *P* ≤ .10 will be included in the multivariate model.

Analysis at a patient level: at this level hierarchal or multilevel methods will be used to take into account the structure of the data and to be able to introduce the variables of the patient in the estimation of the effect of the intervention. The levels will be professional (level 2) and patient (level 1). Multilevel logistic regression models will be made to estimate the effect of the intervention. The strategy of the analysis will be to estimate the effect of the intervention considering professionals as the random part. Afterwards, we will estimate the effect by introducing the variables of quality of care of the professional level (SQPP and SHCQ) and finally, we will study whether the introduction of patient variables modifies the effect of the intervention.

The level of significance will be set at 5% and the statistical package IBM SPSS Statistics v.23.0 for Windows will be used to perform the statistical analyses.

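### Independent tosses for 15 sectors do not secure the 1:1 ratio assumed in the sample size; a restricted, balanced allocation would do better at small cost

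*Protocol article*

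**What the plan says.** The Randomization section of the protocol article makes the sector the unit of allocation ("The randomization will be made by sectors of the ICS") and gives the number of units: "The ICS has 15 sectors". The method is stated as "The sectors will be randomized using a simple randomization method". Each sector receives a random number between 0 and 1, and "the numbers with which the first decimal is <5 will be rounded down to 0 and the remaining will be rounded up to 1". Zeros form the control group and ones the intervention group. The section states no blocking, stratification, matching, or limit on the number or size of sectors per arm.

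The Sample size section plans on "a control versus intervention ratio of 1".

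The Statistical analysis section has a baseline time point before the tool goes live. Its patient-level model estimates the effect in three steps: first with professionals as the random part, then adding the professional's quality-of-care scores (SQPP and SHCQ), then adding patient variables to see whether the effect changes.

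**The concern.** When 15 units are allocated by separate tosses, the number in each arm is random, and a lopsided split is not rare. The sample size takes a balanced ratio as given, so precision can fall short of plan through the draw alone. With so few units, any single draw can also leave the arms unlike each other in size, INR control, event rate or deprivation. All 15 sectors are known in advance, and the database named in the Data collection section holds sociodemographic, clinical and laboratory data on their patients. The imbalance could therefore be limited before allocation. What is at stake is the precision of the effect estimate and how convincing the comparison will look once the baseline tables are seen.

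**Working it through.** **Inputs.** From Randomization: 15 sectors, independent allocation with probability 0.5. From Sample size: ratio 1, power 90% (printed as a weight of 90%), alpha 5%. The plan's own detectable difference (1% at an event rate of 0.66%) can be neither reproduced nor refuted, because no intracluster correlation or design effect is given. The check below therefore concerns only the ratio.

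**Arm sizes.** The number of intervention sectors is Binomial(15, 0.5), with 2^15 = 32,768 equally likely allocations. The number giving split k:(15−k), in either direction, is 2 × C(15,k). Exact 1:1 is impossible with 15 sectors; the closest is 7:8, with 2 × 6,435 = 12,870 allocations.

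**Variance.** With equally weighted sectors, the variance of the arm difference is proportional to 1/k + 1/(15−k). Relative to 7:8 this is 56/[k(15−k)].

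**Power.** Take a two-sided t test on sector summaries with 13 degrees of freedom, and fix the effect so that power is 90% at 7:8 (1.817 between-sector SDs). The noncentrality is 1.817/√(1/k + 1/(15−k)).

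| Split | Allocations | P(this split or worse) | Variance vs 7:8 | Power |
|---|---|---|---|---|
| 7:8 | 12,870 | 100% | 1.00 | 90.0% |
| 6:9 | 10,010 | 60.7% | 1.04 | 88.9% |
| 5:10 | 6,006 | 30.2% | 1.12 | 86.5% |
| 4:11 | 2,730 | 11.8% | 1.27 | 82.0% |
| 3:12 | 910 | 3.5% | 1.56 | 74.0% |
| 2:13 | 210 | 0.7% | 2.15 | 60.0% |

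P(7:8) = 12,870/32,768 = 39.3%. Mean relative efficiency is E[k(15−k)]/56 = 52.5/56 = 0.94, and power averaged over all draws is 87.7%.

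**Patients per arm.** Sector sizes are not given. In simulation with an assumed coefficient of variation of sector size between 0.4 and 0.8, the patient split is worse than 60:40 in 48% to 56% of simple draws, against 10% to 36% when the sector split is held at 7:8.

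**Chance imbalance in a sector characteristic.** The SD of the arm difference, in between-sector SDs, is √(1/7 + 1/8) = 0.52 at 7:8 and 0.54 under simple randomisation. A difference above 0.5 SD occurs in 33% and 35% of draws. Fixing the counts alone therefore hardly changes this; balancing on covariates, or adjusting for them, is what would.

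**What the analysis adjusts for.** The stated effect models contain professionals as a random term, then SQPP and SHCQ, then patient variables. None is said to contain the sector's baseline outcome rate, and no step is named as the primary estimate.

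**The case against.** The strongest reply is that simple randomisation is unbiased, gives 1:1 in expectation, and costs little on average: about 2 points of power. Some 88% of draws have a variance no more than 12% above 7:8. All of this stands. Allocation is also not the main limit on power. For the 10% relative reduction named in the Sample size section (0.66% to 0.594%), two-sided power is about 17% with 63,001 patients and 19% with 73,632, after 10% loss and with no clustering at all.

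Four stronger readings are tempting, and the documents do not support them.

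- A reader might infer that the plan does nothing about imbalance. The staged adjustment is a partial correction, and the listed patient variables include comorbidity, CHA2DS2-VASc and HAS-BLED, which has a labile-INR component.
- A reader might infer that a chance baseline difference would be as large as the effect sought. That depends on the between-sector variation in event rate, which is not given. If its coefficient of variation were 10%, 20% or 30%, the SD of the arm difference at 7:8 would be about 5%, 10% or 16% in relative terms. A difference of 10% or more would then occur in about 5%, 33% or 52% of allocations (normal approximation). The range is too wide to support the claim.
- A reader might infer that such a difference could not be told apart from the effect. A valid sector-level analysis carries chance imbalance in its standard error. Whether the stated two-level model does so is a separate question.
- A reader might count the 0.52 SD against coin tossing. It is the value at 7:8 and comes almost wholly from having 15 units.

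The choice of baseline covariates is also often left to an analysis plan, which is not at hand. The firm part of the point is the allocation method, which the article does fix.

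**Conclusion.** The point holds as a cheap improvement to the design, not as an error of validity. The stated mechanism does not secure the assumed ratio: 7:8 in 39% of draws, 2:1 or worse in 30%, 4:11 or worse in 12%. The loss is small on average and material in the tail, where power is 82% at 4:11 and 74% at 3:12 if it is 90% at 7:8. The probabilities are exact. The variance and power figures assume equally weighted sectors and a sector-level test. Chance imbalance between 15 clusters is a further cost in precision and credibility, which the planned adjustment meets only in part.

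**What to change.** If sectors are not yet allocated, replace the independent tosses with covariate-constrained randomisation:

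1. List the 12,870 allocations with 7 or 8 intervention sectors.
2. Keep those balanced on number of eligible patients, baseline thromboembolic rate, baseline share of VKA patients with TTR <65%, and the MEDEA deprivation index.
3. Draw one of the retained allocations at random.

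Baseline TTR has to be derived from recorded INR values, since the Introduction says the clinical history holds no single variable for INR control.

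If allocation is already done, adjust the primary effect model for the sector's baseline outcome rate. Patient baseline TTR can serve as a covariate only for VKA patients; DOAC patients are also eligible and have no such value.

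The cost is some programming on data the study already plans to extract. The analysis must then account for the constraint, by adjusting for the balancing variables or by a permutation test over the retained allocations. The constraint must also be loose enough that enough allocations remain.
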